**Figure 3 fig3:**
[figure not shown]
Example of expected results regarding postprandial glucose responses to a specific food product related to the individual’s average glucose response. **(A)** A high correlation indicates that postprandial glucose responses to the product are in line with an individual’s average glucose response. **(B)** A low correlation indicates that the postprandial glucose responses to the product deviate from an individual’s average glucose response, suggesting the presence of meal-specific glucose responses.

To estimate the required sample size to be able to detect meal-specific responses, we used preliminary data from 27 participants of the GLYSIMI study (NCT05120661). The GLYSIMI study investigated the role of the human small intestine microbiota in regulating postprandial glucose responses to food products. The study included men and women with a BMI of 25–40 kg/m^2^, aged 40–75 years. During the screening phase of the GLYSIMI study, participants wore a continuous glucose monitor, and glucose responses after seven standardized products at breakfast or dinner were compared. All glucose responses were measured as the iAUC (mg/dl*hour, 120 min postprandially). The average glucose response was calculated as the average glucose response to all products per individual. Correlations between postprandial glucose responses to specific foods and the average postprandial glucose response of an individual ranged between 0.49 and 0.85.

In the RepEAT study, we expect lower correlations between glucose responses to specific food products and the average glucose response, because we measured nine weeks of a fully controlled diet and not only a few standardized meals. Therefore, we expected correlations ranging between 0.3 and 0.4. Using GPower (version 3.1.9.7) and a “Correlation: Point biserial model,” with a two-sided test, an α of 0.05, a power of 0.80, and an effect size of 0.3 and 0.4, this would lead to a required samples size of, respectively, 44 or 82 participants. We chose the average of the two and therefore 57 participants were needed in this study. Considering a 10% drop-out rate, the required sample size was *n*=57 + 6=**63** participants.

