## Results

4

Figure 4 shows a flowchart of the participant enrolment and completion of the RepEAT study. In total, 506 individuals showed interest in the study, of whom 223 were still interested and scheduled for an information session after receiving the written participant information. After having received the written and verbal information, 133 individuals signed the informed consent form and underwent the screening procedure. Of these 133 individuals, 63 individuals were eligible according to all inclusion and exclusion criteria, and were included in the study. During the study, 10 participants dropped out (15.9% drop-out rate) at different stages of the study and for different reasons (depicted in Figure 4). 53 participants completed the study, which is well within the beforehand estimated sample size range of 44–82 participants.

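### The stated requirement of 57 is not the average of 44 and 82 (that is 63), the two sample sizes are listed in reversed order, and 53 completers are judged against the range 44–82 instead of the stated requirement

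*Protocol article*

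**What the plan says.** Section 2.4 (Sample size calculation) sets the effect sizes: "Therefore, we expected correlations ranging between 0.3 and 0.4". It names the method: "Using GPower (version 3.1.9.7) and a “Correlation: Point biserial model,” with a two-sided test, an α of 0.05, a power of 0.80". For effect sizes of 0.3 and 0.4, in that order, it reports that "this would lead to a required samples size of, respectively, 44 or 82 participants". It then combines them: "We chose the average of the two and therefore 57 participants were needed in this study". Six participants are added for 10% drop-out, giving a total of 63.

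Section 4 (Results) reports 63 included, 10 drop-outs (15.9%) and 53 completers, and concludes: "53 participants completed the study, which is well within the beforehand estimated sample size range of 44–82 participants".

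**The concern.** The section gives two numbers and a rule for combining them, and the rule does not produce the printed result. The correct average happens to equal the final enrolment figure, so the 10% allowance disappears if the rule is taken at its word. The list order also implies that the weaker correlation needs fewer participants, which cannot be right.

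Section 4 then sets aside the single requirement of 57 and uses the span 44–82 as the yardstick. Those two values are not the limits of an acceptable range. Each is the requirement under a different assumed correlation, and 44 is enough only if r = 0.4. A reader would conclude that the study ended with adequate numbers, although it finished below its own requirement and has less than 80% power over much of the correlation range it expected.

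**Working it through.** **Inputs (section 2.4).** Point-biserial correlation model, two-sided α = 0.05, power 0.80, r = 0.3 and 0.4; drop-out 10%. From section 4: 63 included, 10 drop-outs, 53 completers.

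**Step 1: reproduce the two components.** Power comes from the noncentral t distribution with df = N − 2 and noncentrality √N · r / √(1 − r²).

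- r = 0.3: 0.3/√0.91 = 0.3145. At N = 82 the noncentrality is 9.055 × 0.3145 = 2.85 and power is 0.803. The smallest N reaching 0.80 is **82**.
- r = 0.4: 0.4/√0.84 = 0.4364. At N = 44 the noncentrality is 6.633 × 0.4364 = 2.89 and power is 0.807. The smallest N reaching 0.80 is **44**.

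Both values reproduce exactly, but attached to the opposite correlations from those the word *respectively* assigns.

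**Step 2: the average.** (44 + 82)/2 = 126/2 = **63**. The document prints 57, a difference of 6.

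**Step 3: other routes to 57.**

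- Harmonic mean: 2 × 44 × 82/126 = 57.3. This is close, but the text does not describe it.
- Geometric mean: √(44 × 82) = 60.1.
- Same model at the midpoint r = 0.35: N = 59.
- Drop-out taken off the true average instead of added: 63 − 6 = 57 (63 × 0.9 = 56.7). This is possible, but not stated.

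**Step 4: drop-out.** The document's sum is 57 + 6 = 63. If the average is 63, enrolling 63 leaves 63 − 63 = 0 for drop-out. Observed drop-out was 10/63 = 15.9%.

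**Step 5: shortfall at completion.** 57 − 53 = **4** against the stated requirement; 63 − 53 = **10** against the true average.

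**Step 6: power by the document's own method, unadjusted α.**

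| N | r = 0.30 | r = 0.35 | r = 0.40 | r needed for 80% power |
|---|---|---|---|---|
| 53 | 0.61 | 0.76 | 0.88 | about 0.366 |
| 57 | 0.65 | 0.79 | 0.90 | about 0.354 |
| 63 | 0.69 | 0.83 | 0.93 | about 0.338 |

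With 53 participants, 80% power is missing from r = 0.30 up to about 0.366, roughly the lower two thirds of the expected range: (0.366 − 0.30)/0.10 = 0.66.

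**The case against.** The strongest reply is that every number is in print (57 required, 53 completed, 10 lost, 15.9%), that 53 does lie between 44 and 82, and that the document openly chose a compromise N without promising 80% power over all of 0.3–0.4. At the midpoint r = 0.35 the loss is modest: 0.79 at 57 against 0.76 at 53. Moreover, 60 participants started the diet and section 3 mentions linear mixed models, so partial data may count; at N = 60 the power is 0.67, 0.81 and 0.91. All of this is fair. It shows that nothing was concealed and that the power figures apply to 53 analysed participants. It does not make 57 the average of 44 and 82, restore the right order, or make 44–82 the requirement.

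A reader might infer four stronger things that the documents do not support.

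- *That 53 is below both computed sample sizes.* It exceeds 44. It is below the stated 57 and the true average of 63.
- *That the plan will read a non-significant correlation as person-specific, so that low power favours the headline finding.* Section 2.4 speaks of low correlations, which is about size; no passage makes non-significance the criterion.
- *That the trial had a target of 70, since 63/0.9 = 70.* No such target was set, and it should not be printed as if it had been.
- *That adding 6 to 57 is itself an error because dividing by 0.9 gives 64.* Adding 10% is a common convention and the difference is one participant.

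**Conclusion.** The point holds as an error in the stated figures. The printed 57 does not follow from the stated rule, which gives 63; the two sample sizes are assigned to the wrong correlations; and the adequacy statement in section 4 uses the wrong comparator. Completion was 4 short of the stated requirement and 10 short of the true average. Power at 53 runs from about 61% to 88% over the expected range.

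The averaging and ordering errors need no assumption beyond the document's own inputs. The power figures assume 53 analysed participants and two-sided α = 0.05 per test. Section 3 plans a Benjamini-Hochberg adjustment, which cannot make the per-test threshold more lenient than 0.05, so these values are not pessimistic in that respect. Whether the slip lies in the number 57 or in calling it an average cannot be settled from the documents.

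**What to change.** Correct the text only; the study is finished and no enrolment is proposed.

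1. In section 2.4, write that correlations of 0.3 and 0.4 require 82 and 44 participants, respectively.
2. In the same section, reconcile 57 with its description. Either correct the average to 63 and state that enrolling 63 left no drop-out allowance, or state how 57 was actually obtained.
3. In section 4, replace the adequacy sentence with: *53 participants completed the study, fewer than the number required by the sample size calculation; at two-sided α = 0.05 before false-discovery-rate adjustment, 53 gives about 61% power at r = 0.30, 76% at r = 0.35 and 88% at r = 0.40, and 80% power only for r of about 0.37 or more.*

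The wording in item 3 fits either choice in item 2, because 53 is below both 57 and 63. The cost is a few sentences and a less favourable statement of power.

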## Statistical analysis

3

Within the RepEAT study, we aim to examine how replicable glucose responses are within individuals and how consistent the variation in glucose responses is between individuals under standardized conditions of a 9-week fully controlled dietary intervention. To determine the replicability of glucose responses to identical meals and food products within individuals, we will compare the three repetitions per meal or food product. To assess the variability in glucose responses to identical meals between individuals, we will compare the three repetitions per product between individuals. Glucose responses will be corrected for metabolic state of insulin sensitivity by using the average glucose response to all meals in the diet and/or the glucose response to the OGTT, and by correcting for physical activity.

IBM SPSS Statistics and the latest R software will be used to carry out the statistical analyses. Numerical values in descriptive statistics will be reported as mean ± SD, categorical values will be reported as numbers and percentages. To determine the normality of the data, a visual inspection of QQ plots and results of the Kolmogorov–Smirnov test will be used. For linear mixed model analyses, model residuals will be checked for normality. Non-normally distributed data will be transformed before the analyses. *p*-values <0.05 will be considered statistically significant.

Glucose responses to single meals will be measured as the incremental area under the curve (iAUC; mg/dl*hour) and will be calculated from the latest timepoint before consumption until 120 min after consumption. In addition, the glucose peak and time to peak will be measured within each postprandial glucose response curve, within 120 min after consumption of a test product. For each meal and food product there will be three repeated measures during the dietary intervention. Glucose responses to single meals will be associated with the average iAUC of all glucose responses of an individual. There will be adjusted for multiple testing using false-discovery rate adjustment according to the Benjamini-Hochberg procedure (32).

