**Discussion:**

The repetitive and fully controlled nature of the dietary study allows detailed assessment of the replicability of the glucose responses to meals and food products within individuals. Furthermore, the consistency of the variation between individuals independent of insulin resistance will be determined.

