#### OGTT and HFMM

2.2.2

To characterize the metabolic response to a meal challenge and to determine insulin resistance, a 7-point oral glucose tolerance test (OGTT) and a high-fat mixed meal (HFMM) test were performed once per individual in the characterization period. The evening before both the OGTT and the HFMM, participants consumed a standardized dinner (24% of energy intake (en%) fat, 54 en% carbohydrates, 22 en% protein; in total 2,380 kJ/565 kcal). After the standardized dinner participants remained fasted until arriving at the research facility. In addition, participants refrained from heavy exercise the evening before and the morning of these tests. Thirty minutes before the start of the test, a venous catheter was placed.

For the OGTT, at *t* = 0 min, participants drank 200 mL of a 75 g glucose solution (Glucomedics, Breda, The Netherlands) within five minutes. Blood was collected in the fasted state before (*t* = 0), and 15, 30, 45, 60, 90, and 120 min after consumption of the glucose solution, to measure plasma glucose and insulin concentrations. The HFMM was provided in the form of a shake and consisted of 320 g water, 20 g protifar, 83.5 g dextrose, 60 g palm olein, and 20 drops of vanilla oil. In total, the shake contained 3,833 kJ and 76.3 g carbohydrates, 17.6 g protein, and 60 g fat (24). To make sure there was no difference in metabolic response due to a difference in consumption speed, participants were instructed to consume the drink in 10 min. Blood samples were collected before consumption (*t* = 0) and 30, 60, 90, 120, 180, and 240 min after the consumption of the HFMM for the measurement of plasma glucose and insulin, free fatty acids, short-chain fatty acids, triglycerides, cholesterol, gut hormones, metabolomics, and proteomics including cytokines. At each time point, the first 2 mL of blood was discarded before drawing the blood samples because it could still contain the physiological salt of the venflon line.

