#### Fasting blood outcomes

2.2.3

Fasting blood samples were collected at baseline, before the start of the OGTT or HFMM, and at the end of the 9-week dietary intervention. Fasting blood was collected to measure glucose homeostasis, oxidative stress markers, plasma concentrations of advanced glycation end-products (AGEs), and immune cell metabolism. We aimed to determine fasting glucose homeostasis by measuring plasma glucose, insulin, and glycated haemoglobin (HbA1c) concentrations after an overnight fast. In addition, fasting blood samples were collected to measure concentrations of oxidative stress markers, and to determine the plasma concentrations of α-dicarbonyls and advanced glycation end-products (AGEs) using ultraperformance liquid chromatography–tandem mass spectrometry. Furthermore, fasting blood samples were used to isolate peripheral blood mononuclear cells (PBMCs) and perform immune cell metabolic profiling using an adapted version of SCENITH (Single Cell Energetic metabolism by profiling Translation inhibition) (25). Additionally, peripheral blood mononuclear cells were stored in Trizol for transcriptomic analysis.

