Up to now, most evidence regarding postprandial glucose responses and variation between and within individuals originates from cohort studies, with only a few standardized meals next to the habitual diet of participants (4, 6, 8). By making use of a fully controlled dietary intervention with continuous glucose and physical activity monitoring, the RepEAT study will provide further insight in the variation in glucose responses independent of external factors such as physical activity, previous meals, and time of day. Moreover, the degree of insulin resistance is an important factor affecting postprandial glucose responses. In the RepEAT study, insulin resistance is determined by an oral glucose tolerance test and will be used to correct for an individual’s insulin resistance status. In addition, all meals were consumed according to a schedule with at least two hours in between meals and snacks to enable us to determine the full glucose response, since on average the glucose concentration returns to baseline within two hours. Furthermore, in order to examine the variation in glucose responses to identical meals and food products within an individual, the 9-week diet consisted of three identical periods of three weeks, resulting in three repetitive measures of postprandial glucose responses to all meals and food products. Given the standardized dietary background, these three repetitive measures per meal and food products will be analysed to measure the robustness of postprandial glucose responses within an individual. Within each three-week period, different versions of the same food product and meal were consumed at the same weekday and time of day, which enables us to study glucose responses to variations of the same food product or meal.

In conclusion, with the RepEAT study we will provide an answer to the question whether person-specific glucose responses to meals are unique and robust enough to be able to be used in personalized advice.

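### The correction labelled insulin sensitivity uses only glucose measures, so it does not by itself support the claim of variation independent of insulin resistance

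*Protocol article*

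**What the plan says.** The Abstract (Discussion paragraph) announces that "the consistency of the variation between individuals independent of insulin resistance will be determined". Section 5 repeats the intention and names the source: "insulin resistance is determined by an oral glucose tolerance test and will be used to correct for an individual’s insulin resistance status".

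Section 3 is the only analysis text that names correction variables. It reads: "Glucose responses will be corrected for metabolic state of insulin sensitivity by using the average glucose response to all meals in the diet", continuing "and/or the glucose response to the OGTT, and by correcting for physical activity".

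Section 2.2.2 gives the purpose of the test, "to determine insulin resistance, a 7-point oral glucose tolerance test (OGTT", and says that blood was drawn at 0, 15, 30, 45, 60, 90 and 120 minutes "to measure plasma glucose and insulin concentrations". Section 2.2.3 adds fasting samples for "measuring plasma glucose, insulin, and glycated haemoglobin (HbA1c) concentrations after an overnight fast".

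Sections 1 and 2.4 define a person-specific response as a departure from the participant's own average response over the nine weeks.

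**The concern.** A glucose curve measures glucose tolerance. It is the joint result of insulin sensitivity, insulin secretion, absorption and other factors. Adjusting for such a curve is a legitimate analysis, but it is not the same as adjusting for insulin sensitivity, and Section 3 labels it as if it were. Section 5 describes the correction as one for OGTT-determined insulin resistance, while Section 3 uses the glucose part of that test only. The and/or also permits three different corrections: average meal response alone, OGTT glucose alone, or both.

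At stake is the wording of one conclusion. If Section 3 is followed as written, a meal response that departs from a participant's average could still partly reflect insulin resistance, yet be reported as independent of it.

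**Working it through.** The plan states no figure on this point, so there is none to reproduce. The check has two parts.

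**1. The statements side by side**

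| Place | Statement | Insulin value used? |
|---|---|---|
| Abstract, Discussion | Variation will be independent of insulin resistance | Not specified |
| Section 5 | OGTT-determined insulin resistance is used to correct | Not specified; no index named |
| Section 3 | Correction by average meal glucose and/or OGTT glucose | No |
| Sections 2.2.2, 2.2.3 | Insulin measured at seven OGTT time points and fasting | Collected |

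The named correction does not use the measurement that would justify the claim, although that measurement was collected.

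**2. How much insulin resistance (IR) could remain**

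The documents do not give the correlation ρ between OGTT glucose and IR. Assume 0.3 to 0.9.

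*Share of the variance of IR itself not captured by OGTT glucose:* 1 − ρ².
- ρ = 0.3: 1 − 0.09 = 0.91
- ρ = 0.5: 1 − 0.25 = 0.75
- ρ = 0.7: 1 − 0.49 = 0.51
- ρ = 0.9: 1 − 0.81 = 0.19

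These are shares of IR variance, not of meal-response variance, and they apply only if OGTT glucose is the sole corrector.

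*Effect on a single-meal response.* Simulation with 20 meals and 20,000 persons; every parameter is an assumption:

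response = b(meal) × IR + 0.7 × person effect + 0.8 × noise

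IR, person effect and noise are standard normal. The slope b averages 0.7 and has an SD between meals of 0 (IR acts equally on all meals), 0.25 (moderate differences) or 0.5 (strong differences). OGTT glucose is IR plus unrelated error. Each meal is regressed on the corrector. The table gives the squared correlation of the residual with IR, averaged over meals.

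| SD of b | Before correction | OGTT glucose alone, ρ = 0.3 / 0.5 / 0.7 / 0.9 | Person's mean alone | Both, ρ = 0.3 / 0.5 / 0.7 / 0.9 |
|---|---|---|---|---|
| 0 | 0.303 | 0.256 / 0.180 / 0.095 / 0.015 | 0.000 | 0.000 throughout |
| 0.25 | 0.296 | 0.254 / 0.185 / 0.090 / 0.015 | 0.017 | 0.016 / 0.013 / 0.008 / 0.002 |
| 0.5 | 0.301 | 0.261 / 0.193 / 0.107 / 0.019 | 0.107 | 0.097 / 0.081 / 0.053 / 0.013 |

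*Hand check of the first row.* Before correction: 0.49 / (0.49 + 0.49 + 0.64) = 0.302. After OGTT glucose alone the expression is 0.49(1 − ρ²)² / [0.49(1 − ρ²) + 0.49 + 0.64]. At ρ = 0.5 this is 0.2756 / 1.4975 = 0.184, against 0.180 simulated.

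The person's mean removes an IR effect that is the same for every meal. It cannot remove one that differs by meal, because the mean mixes IR with other person-level causes and one slope per meal cannot separate them.

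**The case against.** The strongest reply is that correction by the participant's own average is built into the study's question. Someone who responds in line with their average is by definition not person-specific, so removing general glycaemic level is the design and not a defect. That stands. It also means that any part of insulin resistance that raises all meals alike has gone once the average is used.

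It follows that a compensating insulin-resistant participant with an ordinary glucose curve is not automatically misclassified. The outcome is glucose, and such a person has no general elevation to remove. Only an effect that differs between meals could be mistaken for a person-specific response. That stands too.

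A third reply is that Section 5 already provides the insulin-based route ("insulin resistance is determined by an oral glucose tolerance test and will be used to correct for" insulin resistance status) and that an article may leave the choice of index to the full plan. This stands only in part. No finding rests on the index being unnamed in Section 5. The finding is that Section 3 does name its variables, calls them a correction for insulin sensitivity, and specifies the glucose response. Section 5 names no insulin variable that would override that.

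Finally, the comparison of three repetitions within a person is not confounded by a fixed baseline characteristic, so the replicability half of the aim is untouched. That stands.

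**Conclusion.** The point holds in a limited form. Section 3 does not match the Abstract and Section 5, and neither glucose-based corrector justifies saying that the remaining variation is independent of insulin resistance. Insulin resistance can remain:

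- substantially, if OGTT glucose alone is used and tracks insulin resistance poorly (0.26 of single-meal variance at ρ = 0.3, against about 0.30 before correction);
- mainly as a meal-specific effect, if the person's mean is used (0.00, 0.02 or 0.11 with none, moderate or strong differences between meals);
- between 0.00 and 0.10, if both are used.

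These sizes rest wholly on assumed parameters and show the direction and the dependence on the and/or choice. They are not estimates for this trial.

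A reader might infer that insulin resistance necessarily stays in the person-specific variation, or that 51% to 91% of it does. The documents do not support that. The average-response option removes the component common to all meals, and those percentages belong to the OGTT-glucose option alone at assumed correlations of 0.7 to 0.3.

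**What to change.** In Section 3:

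1. Keep the analysis against the participant's average response, since it defines person-specific, but describe it as adjustment for general glycaemic level.
2. For the analysis meant to be independent of insulin resistance, name one index computed from the paired OGTT glucose and insulin values, for example Matsuda. In a pooled model, enter it with an index-by-meal term; as a main effect only, it would leave meal-specific effects of insulin resistance in place. Separate models per meal give the index its own slope in each and serve the same purpose.
3. Replace and/or with one primary choice and list any other as a sensitivity analysis.
4. Align Section 5 with the result.

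If no insulin-based analysis is wanted, limit the Abstract's claim to variation independent of the average glycaemic response.

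The cost is one derived variable, a few sentences, and a few degrees of freedom for the index and its interaction. The insulin measurements are already part of the study, and the article reports the project as still in data cleaning. An index is itself an imperfect measure of insulin resistance, so even the revised analysis should be reported as adjusted for that index.

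If the full analysis plan already specifies such an index, only the wording of Section 3 needs to change.

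### The stated power of 0.80 is for one unadjusted correlation test, but the planned analysis applies Benjamini-Hochberg across meals and products

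*Protocol article*

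**What the plan says.** Section 2.4 (Sample size calculation) plans to identify person-specific responses by correlating the response to a meal or product with the participant's own average over the nine weeks. It uses the G*Power point-biserial correlation model "with a two-sided test, an α of 0.05, a power of 0.80, and an effect size of 0.3 and 0.4". The two effect sizes come from this statement: "Therefore, we expected correlations ranging between 0.3 and 0.4". The results are given as "an effect size of 0.3 and 0.4, this would lead to a required samples size of, respectively, 44 or 82 participants", followed by "We chose the average of the two and therefore 57 participants were needed in this study". An allowance for drop-out brings the target to 63.

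Section 3 (Statistical analysis) sets 0.05 as the significance threshold, relates single-meal responses to the average iAUC of all the participant's responses, and adds: "There will be adjusted for multiple testing using false-discovery rate adjustment according to the Benjamini-Hochberg procedure". It does not say how many tests form the adjusted family, and section 2.4 does not mention multiplicity. Section 4 (Results) reports 53 completers and describes that number as falling inside the 44 to 82 range.

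**The concern.** The power figure and the analysis describe two different procedures. A single test at 0.05 rejects whenever its p-value is below 0.05. Under Benjamini-Hochberg with m tests of which k are rejected, the cut-off is 0.05 × k/m. That equals 0.05 only if every test is rejected, and is lower otherwise. Average power per product therefore cannot exceed the single-test figure and will usually be lower.

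At stake is how readers judge the design. They will take 0.80 as the chance of detecting a correlation of the planned size in the analysis that will be reported. They will also take the 44 to 82 range, against which the 53 completers are judged, as adequate for that analysis. Both rest on the unadjusted calculation.

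**Working it through.** **Inputs from the protocol article.** Section 2.4: two-sided alpha 0.05, power 0.80, r = 0.3 and 0.4, point-biserial model, n = 57 before drop-out. Section 3: Benjamini-Hochberg, threshold 0.05. Section 4: 53 completers, 378 meals each.

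**Assumptions, because the document gives no figure.** The false-discovery rate is q = 0.05. The number of tests is large; 378 meals / 3 repetitions = 126 is an upper bound. The share of products with a non-zero correlation, π, is 1 (all) or 0.5 (half). Non-null products share the same r, and tests are independent given the average response.

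**Step 1: reproduce the plan's figure.** Single-test power comes from the noncentral t with n − 2 degrees of freedom and noncentrality √n × r/√(1 − r²).
- n=82, r=0.3: noncentrality 2.848, power 0.803.
- n=44, r=0.4: noncentrality 2.895, power 0.807.

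Both printed sizes reproduce, so they contain no allowance for multiplicity. (The text pairs them with the effect sizes in reverse order: 82 belongs to 0.3 and 44 to 0.4.)

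**Step 2: single-test power at the sizes actually used.**
- n=57: 0.645 (r=0.3), 0.90 (r=0.4).
- n=53: 0.61 (r=0.3), 0.88 (r=0.4).

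**Step 3: average power under Benjamini-Hochberg.** With many tests, the effective cut-off t solves t = q × [(1 − π) × t + π × power(t)], where power(t) is the power in Step 1 at two-sided level t. For n=57, r=0.3, π=1 the solution is t = 0.0272: power(0.0272) = 0.545, and 0.05 × 0.545 = 0.0272.

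| n | r | Single test | All correlated | Half correlated |
|---|---|---|---|---|
| 82 | 0.3 | 0.80 | 0.77 | 0.66 |
| 44 | 0.4 | 0.81 | 0.77 | 0.66 |
| 57 | 0.3 | 0.645 | 0.55 | 0.39 |
| 57 | 0.4 | 0.90 | 0.89 | 0.82 |
| 53 | 0.3 | 0.61 | 0.50 | 0.34 |
| 53 | 0.4 | 0.88 | 0.86 | 0.78 |

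At the midpoint r=0.35 with all products correlated, power goes from 0.79 to 0.75 at n=57 and from 0.76 to 0.71 at n=53.

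**Step 4: check by simulation.** Tests sharing one average-response variable were simulated at n=57 for 7, 20, 50 and 126 products. With all correlated, average power was 0.52 to 0.54 (r=0.3) and about 0.87 (r=0.4). With half correlated and 20 or more products, it was 0.38 to 0.41 and 0.78 to 0.80. These run slightly below the table, as does simulated single-test power (about 0.63 and 0.88). With all correlated, the number of products hardly matters.

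**Step 5: split the shortfall at n=57, r=0.3, all correlated.** From 0.80 to 0.545 is 0.255. The choice of n accounts for 0.80 − 0.645 = 0.155, about 61%. Benjamini-Hochberg accounts for 0.645 − 0.545 = 0.10, about 39%.

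**The case against.** The strongest reply is that the adjustment costs little under the protocol's own expectation. Section 2.4 expects correlations of 0.3 to 0.4 and names no null products. At the sample sizes to which 0.80 is attached, the loss is then about 3 points, and at n=57, r=0.4 it is about 1 point. The preliminary correlations were higher still, 0.49 to 0.85; at r=0.49 adjusted power is about 0.98 at n=53 even before any further allowance. Each product also contributes to the average it is compared with, which makes exact zeros less likely. All of this stands. The half-correlated column is therefore a sensitivity figure and not an expectation.

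Three stronger readings are tempting, and the document does not support them:
- **That Benjamini-Hochberg explains the whole gap from 0.80.** Step 5 shows it does not. The protocol also does not state 0.80 at n=57; that n is described as the average of 44 and 82, which is 63. This is a separate matter.
- **That lost power will make more products count as person-specific.** Section 2.4 ties that reading to a low correlation, that is, to the size of the coefficient. Nowhere is a non-significant adjusted p-value given that meaning, and the adjustment leaves estimated correlations unchanged.
- **That every test faces a cut-off below 0.05.** The step-up cut-off is at most 0.05 and reaches it when all tests are rejected.

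It can also be said that defining the family of tests is often left to an analysis plan, and that quoting single-test power alongside false-discovery control is common. The first is fair, and the undefined family is not raised here as a fault in itself. The second does not make the printed figure the power of the printed analysis.

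**Conclusion.** The point holds. The 0.80 is the power of one unadjusted test, and the analysis in section 3 is adjusted. If every product is correlated, the loss due to the adjustment alone is about 3 points at the design points, about 10 points at n=57 with r=0.3, and about 1 point at n=57 with r=0.4. At n=53 it is about 12 points (0.613 to 0.495) and about 1 point. If only half are correlated, adjusted power at n=57 is about 0.39 (r=0.3) and 0.82 (r=0.4); at n=53 it is 0.34 and 0.78.

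These figures rest on q=0.05, many tests, a common r, and independence given the average. The share of non-null products is an assumption throughout. The point concerns how power is stated. It does not show that the analysis is invalid or that its conclusions will be pushed in one direction.

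**What to change.** In section 2.4, label 0.80 as the power of a single unadjusted test. Add the average power per product under Benjamini-Hochberg at the n actually used (57 planned, 53 completed), for r=0.3 and r=0.4. State with it the number of products in the tested family, the false-discovery rate, and a range for the share of non-null products, for example half to all.

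The cost is a short recalculation and a less favourable stated power. The study has been conducted, so no participants are added and the analysis itself does not change.
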